**2.8 Proposed primary and secondary outcome measures**

Primary objective: To determine if short daily hemofiltration, compared to conventional hemodialysis, is associated with a sustained (> 3months) improvement in systolic blood pressure.

Secondary objectives: 1) To determine if the mechanism by which short daily hemofiltration is associated with an improvement in blood pressure control is secondary to changes in sympathetic nervous system and/ or extracellular fluid volume 2) To determine if short daily hemofiltration, compared to conventional hemodialysis maintains metabolic homeostasis (serum calcium, phosphate, potassium and bicarbonate), and 3) To determine patient modality preference.

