**1.3h DAILY HEMOFILTRATION – Our preliminary pilot data**

Daily hemofiltration has the potential to combine the benefits of both short daily hemodialysis and conventional hemofiltration. However, experience with daily hemofiltration outside of the intensive care unit is limited. We undertook a pilot project using a new system developed by NxStage Medical (Lawrence, MA). The system consists of a simple portable microprocessor controlled cycler for therapy administration and a disposable cartridge for blood and fluid handling (Appendix 1,2). The system is used with pre-packaged solutions much like peritoneal dialysis such that additional plumbing and water requirements are not necessary in the home. Because of the simplicity of the system, patient training time is reduced to approximately 3 weeks.

For the purposes of our prospective pilot study, urea clearance was targeted at 0.40+/-0.5 per treatment 6 days a week in keeping with a standard Kt/V of 2.0. In spite of the lower weekly urea clearance delivered, the patients experienced a reduction blood pressure (Table 1), a 50% reduction in the number of antihypertensive medications, an improvement in quality of life, and in beta-2-microglobulin levels, a marker of middle molecular weight clearance (19,20). However, the study duration was too short to determine if the improvement in blood pressure will be maintained in the long term. In addition, we did not explore the mechanism(s) by which the blood pressure was improved.

Table 1: Improvements in Blood Pressure with Daily Hemofiltration (6x/week) Compared to Conventional Hemodialysis N=7

| Pre Treatment Pressure | Hemodialysis | Hemofiltration | p-value |
| --- | --- | --- | --- |
| Mean Arterial Pressure (mmHg) | 96 (±11) | 86 (±12) | 0.001 |
| Systolic Blood Pressure  (mmHg) | 139 (±18) | 128 (±19) | 0.001 |
| Diastolic Blood Pressure  (mmHg) | 74 (± 9) | 66 (±11) | 0.01 |

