**2.9d SYMPATHETIC NERVE ACTIVITY**

As previously described by the co-applicant (MR), postganglionic multifibre muscle sympathetic nerve activity will be recorded microneurographically using a sterile tungsten microelectrode with a shaft diameter of 200 μm and a non-insulated tip of 5 μm in diameter inserted into a muscle fascicle of the peroneal nerve posterior to the fibular head. A reference electrode is inserted subcutaneously 1 – 2 cm from the recording electrode. Electrodes will be connected to the remote, low noise preamplifier of the Nerve Traffic Analyzer, (University of Iowa, Iowa City, Iowa). The neural signal will be amplified by 40,000, input to a bandpass filter (0.5 to 1 KHz) and integrated to obtain a mean voltage neurogram. The mean voltage neurogram, ECG, respirations and BP signals will be digitized with a sampling frequency of 2,000 to 5,000 Hz, and recorded on a Ponemah Data Acquisition System (Gould, Valley View, OH). Pulse synchronicity and low signal-to-noise ratio will confirm burst activity as being of muscle sympathetic efferent origin. MSNA (burst/min and bursts/100 beats) will be calculated from 10-minute recordings after 20 minutes of rest. Muscle sympathetic nerve activity recordings will be performed at the time of randomization, after the first 3 months of the cross-over phase and again at study completion when the patient is at their dry weight.

**2.10 What is the proposed sample size?** 20 patients. Based on our previous pilot study, assuming a standard deviation of 11, an alpha = 0.05, we will have 80% power to detect a difference of 11 between the groups.

**2.11 Planned recruitment rate –** Patients will be recruited from the ~ 600 patients undergoing in-centre hemodialysis at the Ottawa Hospital. Due to limited access to the machines for hemofiltration a maximum of 10 patients can be treated in each 6 month period. Allowing for upfront recruitment and training time, it is anticipated that it will take 18 months to recruit all of the patients with a further six months after the last patient is recruited to complete the study. Data analysis and manuscript preparation are expected to take an additional 6 months.

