**2.12** **Anticipated compliance and loss to follow-up problems –** Reported drop out rates from daily dialysis programs are low. In our own home hemodialysis program, only 1 patient out of 20 has chosen to return to conventional hemodialysis after completing training. In our one-month pilot study of daily hemofiltration, one patient dropped out of the study due to an adverse event. Given the longer duration of follow-up and the requirement for an in-centre protocol, we anticipate 2 patients may drop out of the study. Furthermore, we don’t anticipate any loss to follow-up as end stage renal disease patients require dialysis as a life saving procedure. However, patients may decide to withdraw from the study.

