**2.13 Proposed type of analysis**

The primary analysis, using a t-test, will be a comparison of mean pre-dialysis systolic blood pressure values from the last month on hemodialysis and the last month on hemofiltration. As described by Zoccali et al, this will give us an assessment of the pressure load as experienced by the left ventricle (92). Supporting analytic and descriptive analysis will be carried out to ensure Consort guidelines can be followed for publication of results.

Continuous outcomes measures for the secondary analysis will be analyzed in exactly the same manner. All efforts will be made to minimize missing values. A sensitivity analysis under extreme but reasonable assumptions will be carried out to evaluate the impact of any missing values.

Lastly, linear regression will be undertaken with systolic pressure as the dependent variable. Treatment type, extracellular fluid volume and sympathetic nervous system activity will be examined for their independent effects on blood pressure control.

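### Secondary objective 2 asks whether hemofiltration maintains metabolic control, but the planned difference t-test can support that only by failing to reach significance

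*Protocol*

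**What the plan says.** Protocol section 2.8 lists as secondary objective 2 whether short daily hemofiltration (HF) "compared to conventional hemodialysis maintains metabolic homeostasis (serum calcium, phosphate, potassium and bicarbonate"), the comparator being conventional hemodialysis (HD).

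Section 2.13 fixes the primary method: "The primary analysis, using a t-test, will be a comparison of mean pre-dialysis systolic blood pressure values from the last month on hemodialysis", set against the corresponding month on HF. On the other outcomes it states: "Continuous outcomes measures for the secondary analysis will be analyzed in exactly the same manner". It does not say whether the t-test is paired.

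No margin, reference range, CI rule or definition is attached to "maintains metabolic homeostasis".

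Section 2.10 sets the sample size at 20 from the pilot data, on this basis: "assuming a standard deviation of 11, an alpha = 0.05, we will have 80% power to detect a difference of 11 between the groups". That calculation concerns systolic pressure only. Section 2.12 adds "we anticipate 2 patients may drop out of the study".

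Laboratory tests are monthly (section 2.9), so a last-month comparison uses about one value per patient per period.

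**The concern.** The objective asks for evidence of no important change. The chosen test looks for evidence of a change. If it does not reject, that is compatible both with maintained control and with a worsening that the trial was too small to see. If it does reject, the shift may still be too small to matter. Noisier data make non-rejection more likely, so the result that looks favourable to HF becomes easier to obtain as the information gets poorer.

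The question is not idle. Section 1.3g itself says that hemofiltration usually clears small molecules less well than hemodialysis. Section 1.5 expects the results to help establish daily HF as an acceptable alternative and, if the primary hypothesis holds, to support an application for a larger trial. An unsupported statement that potassium or phosphate was maintained could carry forward into that work.

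**Working it through.** **1. The plan's own figure.** Inputs from section 2.10: SD 11, difference 11, alpha 0.05, power 80%. Read as a paired two-sided t-test with SD 11 in each period and no correlation between periods, the SD of the difference is 11 × √2 = 15.6 and the standardized effect is 11 / 15.6 = 0.707. Exact noncentral-t power at n = 18 is 80.7%, and 18 + 2 dropouts = 20. Two other readings do not give 20: if 11 is the SD of the within-patient difference, n = 10; a two-sample exact t-test needs 17 per arm. The protocol does not say which is meant. None of these readings involves the laboratory values.

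**2. Set-up for objective 2.** n = 20 − 2 = 18 completers. The protocol gives no laboratory SDs, so everything is in units of SD_d, the SD of the within-patient HF−HD difference. Assumptions: paired t, two-sided 5%, 17 degrees of freedom, critical value 2.110.

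**3. Precision.** CI half-width = 2.110 × SD_d / √18 = 0.497 SD_d, about 0.50 SD_d. With all 20 patients it is 2.093 / √20 = 0.47 SD_d. As an illustration only, if SD_d for potassium were 0.4 to 0.8 mmol/L (assumed), the half-width would be 0.20 to 0.40 mmol/L.

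**4. What non-significance and a limit-based rule would deliver at n = 18.** Noncentrality = δ × √18, where δ is the true worsening in SD_d. For δ = 0.5 this is 2.12, almost equal to the critical value, so the test is close to a coin toss. The last two columns assume a true difference of zero and ask how often the 95% CI lies inside the limit.

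| Worsening or limit (SD_d) | Non-significant if HF is truly worse by this much | CI inside a one-sided limit of this size | CI inside limits of this size on both sides |
|---|---|---|---|
| 0.3 | 78% | 22% | under 1% |
| 0.4 | 64% | 36% | 2% |
| 0.5 | 48% | 52% | 13% |
| 0.6 | 33% | 67% | 36% |
| 0.7 | 20% | 80% | 60% |
| 0.8 | 11% | 89% | 78% |

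Columns two and three are exact noncentral-t results. Column four is by simulation.

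**5. Sensitivity.** With all 20 patients, a true 0.5 SD_d worsening is still non-significant 44% of the time. If the t-test were unpaired with 18 values per period, a true shift of 0.5 between-patient SD would be non-significant 69% of the time. Patients needed for 80% power with a one-sided limit: 34 at 0.5 SD_d, 90 at 0.3 SD_d.

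**The case against.** The strongest reply is that section 2.13 names a test and not a decision rule, that it also promises supporting descriptive analyses, and that definitions and margins usually sit in an analysis plan, which is not at hand. Part of this stands. A reader might infer that the investigators intend to report a non-significant result as maintained control; the protocol never says so. What remains is that the protocol does not leave the method open. It prescribes one, and an analysis plan that follows it inherits a test that cannot answer the objective.

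A second reply is that nothing shows the precision to be inadequate, because no limit is stated and the SDs are unknown. That is fair, and it is why the results are standardized. It is also part of the problem: without a limit, no result can establish maintenance.

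Third, homeostasis is not purely a question of non-inferiority. Calcium and bicarbonate can depart in either direction, so a single harmful side does not suit every analyte. This stands and shapes the fix.

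Some stronger readings are tempting, and the documents do not support them:

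- Summing session Kt/V gives 6 × 0.5 = 3.0 a week on HF against 3 × 1.2 to 3 × 1.4 = 3.6 to 4.2 on HD, which suggests a lower dose on HF. Section 2.2 describes the two prescriptions as about equal in standard Kt/V, and section 1.3d explains why session sums mislead when frequency changes.
- The lower urea clearance in section 1.3h belongs to the pilot, which targeted 0.40 per treatment; this trial targets 0.50.
- The potassium value of 6.6 mEq/L in section 2.5 is an eligibility criterion, not an outcome threshold.

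The fourth amendment, listed at the end of the protocol, records a switch to daily hemodialysis. As described there, it changes neither this objective nor its analysis, so the mismatch applies to whichever daily modality is compared.

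**Conclusion.** The point holds as a mismatch between a stated objective and its stated test. At about 18 completers, a worsening of half an SD of the within-patient difference would escape detection roughly half the time (48%), and one of 0.3 SD about 78% of the time, so a non-significant result says little about maintenance. These figures rest on a paired two-sided 5% t-test, 2 dropouts and standardized effects; an unpaired test would be less sensitive.

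The consequence is limited to a secondary objective. The systolic pressure comparison is unaffected. The change should be made, but the trial does not depend on it.

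**What to change.** - For each of the four analytes, report the within-patient HF−HD difference with its 95% CI. Keep the last-month comparison. If more monthly values are used, omit those drawn at or soon after the switch: section 2.9 describes no washout, and early values may still reflect the previous modality and pull the difference toward zero.
- Have the investigators fix, before unblinding, the largest departure they would accept for each analyte, on both sides where either direction matters. Conclude maintained only if the CI lies within those limits; otherwise give the estimate descriptively and state that maintenance was not shown. Section 2.4 already plans for blinded analysts, so the limits can be set in time.
- Report calcium- and phosphate-related medication use by modality alongside. Section 2.9 adjusts medication to targets during the run-in, and if this continues in the crossover it would draw the serum comparisons toward no difference.

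The cost is revised analysis wording and agreement on the limits; the data are already collected. The real downside is that maintenance becomes harder to claim. With 18 patients and no true difference, a one-sided limit must be about 0.7 SD or wider for 80% power. Two-sided limits must be wider still (78% at 0.8 SD). Not shown is therefore a likely result for some analytes, and the protocol should say so in advance.

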**2.9 Measurement of outcomes at follow-up (Appendix 3)**

After providing informed consent, baseline medication use will be recorded and the comorbidity score (Charleson) calculated. Laboratory values including the standard hemoglobin, calcium, phosphate, albumin, electrolytes, creatinine, and urea, will be measured at study entry. Each patient will continue hemodialysis for an additional 3 months. During that time, the patient’s Kt/V will be adjusted to 1.2-1.4. If the Kt/V is too high, the prescribed blood pump speed will be reduced. If necessary, the patient’s current dialyzer will be exchanged for a different polysulfone dialyzer with a lower urea clearance. Lastly, the patient’s time may be decreased by a maximum of 30 minutes as long as this does not interfere with fluid removal (mimic the HEMO study). During this time because of the effects on muscle sympathetic nervous system activity, any patients who are taking sympatholytics, angiotensin converting enzyme inhibitors or angiotensin receptor blockers will have these medications weaned. If the patient’s blood pressure increases to greater than 165/95, metoprolol, long acting dihydropyriding calcium channel blocker and / or non-dihydropyridine calcium channel blocker (with known minimal effect on central sympathetic outflow) will be introduced (Appendix 4). All patients will have their dry weight adjusted in an attempt to decrease blood pressure pre-dialysis to <140/90). Standard laboratory tests will be repeated monthly (first Wednesday or Thursday) and medications adjusted to meet currently accepted targets for hemoglobin, calcium and phosphate (Appendix 5). The prior 3 months of hemodialysis therapy, within a clinical trial setting, will ensure optimal management of blood pressure prior to starting hemofiltration to ensure that any improvements in BP on daily HF are secondary to modality and not more intensive intervention from health care providers*.*

After the completion of the 3 month hemodialysis run in phase, patients will be randomized to either to a further 3 months of hemodialysis or 3 months of hemofiltration. The starting prescription for hemofiltration will be enough replacement fluid (Hemosol) to achieve a daily (6 days/week) treatment Kt/V of 0.50 (±0.05). Each treatment will take approximately 2-2.5 hours and will occur during the day in centre. Remaining in-centre for the duration of the study avoids the potential bias of typically lower blood pressures at home compared to the clinic environment. The starting prescription for hemodialysis will be unchanged from the preceding 3 months (3 days/week, approximately 3.5-4 hours per treatment). Each patient will undergo measurement of their extracellular fluid volume using bioelectrical impedance, sympathetic nervous system activity using microneurography and ambulatory 24-hour blood pressure measurements (during an off treatment day) prior to the start of and at the end of this 3 month phase. Additionally, each patient will have the standard laboratory investigations repeated on the first Wednesday/Thursday of the month. The nurses will document vitals pre and post each treatment session. Medications, and any adverse events including hospitalizations will be reassessed at the time of monthly blood work.

After completing the 3 months of hemofiltration or hemodialysis, patients will then switch treatment modality for a further 3 months. The same protocol will be followed for laboratory investigations, assessment of vitals, medications and adverse events as during the preceding 3 months. Repeat extracellular fluid volume measurement, muscle sympathetic nerve activity and ambulatory blood pressure recordings will be completed at the end of the study.

**2.9a BLOOD PRESSURE MEASUREMENTS**

Blood pressure will be measured pre and post dialysis as recommended by the Canadian Hypertension Society (www.hypertension.ca). Briefly, the patient will have their back supported, feet on the floor and will sit quietly for 5 minutes. The arm will be supported and a mercury sphygmomanometer will be used*.* An appropriate sized cuff will be placed at the level of the heart and inflated to 20mmHg above the level at which the radial pulse disappears. Phase I Korotkoff, appearance of first sound, will be taken as the systolic blood pressure and phase V Korotkoff, disappearance of sound, will be taken as the diastolic blood pressure. Two measurements will be taken and averaged. Patients will be discouraged from using alcohol, caffeine, or tobacco within one hour of BP measurement. The measurements will be taken in the arm opposite to the one with a functioning access (if a central venous catheter is in place, the non-dominant arm will be used) prior to needle insertion for the hemodialysis/hemofiltration treatment.

Ambulatory blood pressures will be performed with a portable oscillometric recorder (Spacelabs 90207). Recordings will begin after the completion of hemodialysis and hemofiltration and will continue for a 44 hour period (the time between treatments) on three different occasions (at the time of randomization, after the first 3 months of the cross-over phase and again at study completion). The pressure will be measured every 30 minutes. The most appropriate cuff will be selected from the 4 sizes supplied by the manufacturer Sleep times will be determined from patient’s diaries. Nocturnal hypertension will be defined as the absence of a decrease of blood pressure during sleep by 10% compared to the awake period. If fewer than 75% of the potential readings are recorded or if more than 90 minutes lapses without a valid blood pressure recording, the ambulatory session will be repeated in 7 days.

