# Measurement of blood pressure for patients on hemodialysis

Accurate blood pressure measurements in hemodialysis units are difficult. Rahman et al compared ‘usual’ blood pressure measurements in 270 hemodialysis patients compared to those blood pressures measured using the standardized American Heart Association protocol. The pre-dialysis usual blood pressure measurement over estimated systolic/diastolic blood pressure by 14.3/7mmHg emphasizing the need for standardized measurements (49). Similar results have been seen with ambulatory blood pressure measurements. However, an average of 2 weeks of pre-dialysis blood pressure of >150/85 has a sensitivity of 80% in the diagnosis of hypertension compared to ambulatory blood pressure measurements (50). Additionally, an average of 4 weeks of pre-dialysis blood pressures when compared to ambulatory blood pressure monitoring is equally effective in explaining the variance in LV mass (51,52). However, the average blood pressure measurement does not allow for the assessment of non-dipping of nocturnal blood pressure that has been associated with an increase in LV diameter and mortality in ESRD patients (53-56).

In summary, although ambulatory blood pressure monitoring allows for a more complete assessment of hypertension, an average of 2-4 weeks of pre-dialysis blood pressure appears to be an effective alterative for routine monitoring of blood pressure. Additionally, the use of standardized techniques for blood pressure measurement are critical to avoid mislabeling of patients.

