**2.2 Planned trial interventions**

The study will be a 9-month randomized, unblinded, crossover trial of patients comparing short daily (6 days/week) in-centre hemofiltration with a spKt/V (measure of dialysis adequacy: sp=single pool, K= dialyzer clearance of urea, t= time on dialysis, V=volume of urea distribution) of 0.5 (±0.05) to conventional hemodialysis with a spKt/V of 1.2-1.4 yielding approximately equivalent standard Kt/V measurements. A pre and post treatment blood pressure will be measured each treatment, using standard techniques (*see below*). The number, type and strength of antihypertensive medications will be recorded at study entry and at the beginning of each month. Standard laboratory parameters for metabolic control (hemoglobin, calcium, phosphate, albumin, electrolytes, creatinine and urea) will be collected monthly. Additionally, each patient will have an assessment of extracellular fluid volume via bioimpedance, sympathetic nervous system activity via muscle sympathetic nerve activity and ambulatory blood pressure monitoring on 3 separate occasions.

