**2.4 Methods for protecting against sources of bias**

Patients cannot be blinded to the hemofiltration modality. However, the final data analysis will be by individuals who are blinded to the patient’s therapy. Nurses who are unaware of the objectives of the study will take vital signs with an automated blood pressure cuff. Ambulatory blood pressure monitoring and muscle sympathetic nerve activity recordings are unlikely to be affected by patient knowledge of treatment modality.

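### Sections 2.4 and 2.9a of the protocol give two different devices for the primary blood pressure reading, and following 2.9a removes the one listed safeguard that takes observer judgement out of it

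*Protocol*

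**What the plan says.** Section 2.4 (protection against bias) states: "Nurses who are unaware of the objectives of the study will take vital signs with an automated blood pressure cuff".

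Section 2.9a opens with "Blood pressure will be measured pre and post dialysis as recommended by the Canadian Hypertension Society" and then sets out a manual procedure: "The arm will be supported and a mercury sphygmomanometer will be used", and "Phase I Korotkoff, appearance of first sound, will be taken as the systolic blood pressure". It also asks for five minutes of seated rest, arm support, a suitable cuff size and the average of two readings.

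Both sections concern the same readings. Section 2.2 calls for a pressure before and after every treatment by standard techniques and points forward to their description. Section 2.9 adds "The nurses will document vitals pre and post each treatment session". Section 2.13 defines the primary analysis as a "comparison of mean pre-dialysis systolic blood pressure values from the last month on hemodialysis and the last month on hemofiltration". Section 2.2 also fixes the design: "The study will be a 9-month randomized, unblinded, crossover trial of patients".

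**The concern.** Section 2.9a is a complete auscultatory method, including how far to inflate the cuff and which sounds mark systolic and diastolic pressure. It is not a loose device name that could cover an automated monitor. A nurse cannot follow it and section 2.4 in the same reading.

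The device matters because the treatment is open. With auscultation, the observer decides when the first sound appears, and that observer can see which modality the patient is receiving. An automated cuff takes that decision away. If the unit follows 2.9a, the trial loses a protection that its bias section claims. If some staff follow one section and some the other, the endpoint mixes two methods, and nothing in the protocol controls or records the mix.

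**Working it through.** **Do the two sections describe different readings?** Three ways out were checked.

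- *Ambulatory monitoring.* The automated cuff in 2.4 is not the ambulatory recorder. Section 2.4 treats ambulatory monitoring in its own sentence, and 2.9a describes the oscillometric recorder in its own paragraph.
- *Vital signs as something separate.* Section 2.9 has the nurses record vitals around each session, and section 2.2 sends the pre- and post-treatment pressures to the technique in 2.9a. No second set of nurse readings is described.
- *Amendments.* The four listed amendments concern self-care, eligibility pressures with added catecholamines, the Kt/V adjustment, and the switch to daily hemodialysis. None concerns the blood pressure device.

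The conflict therefore stands, and it falls on the primary endpoint.

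**What would each pattern of use do to the treatment difference?** Let *d* be the mean mercury-minus-automated difference (not given in the protocol), and let *p*₁ and *p*₂ be the shares of mercury readings in the last month on the daily treatment and on conventional hemodialysis.

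- The bias from mixing is *d* × (*p*₁ − *p*₂).
- One device throughout: *p*₁ = *p*₂, so the bias is 0 and a constant offset cancels within the patient.
- Mixed use unrelated to modality: the expected bias is 0, but the spread of the readings grows.
- Mixed use that differs by modality: the bias is not 0, and without a record of the device it cannot be separated from the treatment effect.
- Mercury throughout: the offset cancels, but any difference in how observers read the two modalities does not.

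**Scale.** The only figure on technique is in the background section on blood pressure measurement: usual pre-dialysis readings "over estimated systolic/diastolic blood pressure by 14.3/7mmHg" relative to a standardized protocol. Against the target difference in section 2.10, 14.3 / 11 = 1.3. This is not a value for *d*.

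**Illustration with assumed biases.** First, the plan's own figure. Section 2.10 gives 20 patients, SD 11, alpha 0.05 and 80% power for 11 mmHg. With a two-sided paired t-test and SD 11 per treatment with no within-patient correlation (an assumption), the SD of the difference is 11 × √2 = 15.6. Then 18 completers give 80.7% power, and the 2 dropouts anticipated in section 2.12 bring this to 20. If 11 is instead the SD of the difference, 10 patients give 80.3% and 20 give 98.9%. The protocol does not say which is meant, so both are carried.

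Now suppose no true effect, n = 20, and a reading bias *b* that differs between modalities. The chance of a significant result in the biased direction comes from the noncentral t with 19 degrees of freedom and noncentrality *b* / (SD / √20). For *b* = 2 and SD 15.6, that is 2 / 3.48 = 0.57.

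| Assumed *b* (mmHg) | SD of difference 15.6 | SD of difference 11 |
| --- | --- | --- |
| 0 | 2.5% | 2.5% |
| 2 | 7.9% | 11.8% |
| 3 | 12.7% | 21.1% |
| 5 | 27.6% | 48.8% |

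The values of *b* are chosen, not estimated. The table shows only that a modest modality-dependent error would matter in a trial of this size.

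**The case against.** The strongest reply is that a crossover protects itself. Section 2.9 keeps all treatment in-centre, expressly to avoid a setting effect on blood pressure, and applies the same protocol for vitals after the switch. Section 2.9a gives one procedure for both modalities. If a single device is used, its offset largely cancels. That stands: the documents give no reason to expect device use to differ by modality, and a reader who inferred that it would do so would be going beyond them.

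A reader might also infer that the protection in section 2.4 disappears altogether. It does not. The nurses are not told the aims, the final analysis is blinded, and ambulatory recordings at randomization and at the end of each period give an observer-independent check. But blinded analysis cannot correct a reading that was biased when taken, ambulatory pressure is not the primary endpoint, and nurses unaware of the aims still see the modality. Digit preference alone, if equal in both periods, is not a treatment bias.

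Finally, a reader might multiply 14.3 mmHg by the share of readings taken with the other device and call the product the bias. The documents do not support this. That figure compares unstandardized with standardized technique, and section 2.2 asks for standard technique throughout.

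**Conclusion.** The contradiction is certain, concerns the primary endpoint, and is not resolved elsewhere in the protocol. As written, the plan cannot be followed. Following 2.9a gives up the one listed protection that removes observer judgement from the primary reading, and the other protections make up for this only in part. Using both devices adds noise, and adds bias if the mix differs by modality.

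The size of any bias is unknown. The documents support only the statement that technique can shift systolic pressure on the scale of the 11 mmHg target. The concern about observer bias is an inference. It rests on auscultation depending on the observer and on nurses being able to see the treatment, and it does not assume that biased reading will occur.

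**What to change.** Reconcile sections 2.4 and 2.9a so that one device and one procedure apply to every primary-endpoint reading in both periods. The automated cuff is the better choice because the protocol's own case against bias relies on it:

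- replace the mercury and Korotkoff text in 2.9a with the automated device;
- use the same device model and cuff size for each patient throughout;
- keep the five-minute seated rest, arm support and mean of two readings.

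The cost is protocol wording, since an automated cuff is already in the plan. There is a small downside: this departs from the auscultatory procedure that 2.9a attributes to the Canadian Hypertension Society, and values will be less comparable with auscultatory studies.

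If mercury is kept instead, delete the automated cuff from the safeguards in 2.4 and state there that a risk of observer bias remains. Either choice removes the contradiction; only the first keeps the safeguard.
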